7.5. Concomitant and supportive therapy

7.5.1. Concomitant therapy that will not be permitted (prohibited concomitant therapy)

None of the following therapies will be performed during the protocol treatment or follow-up until relapse or secondary cancer is confirmed.

1) Antineoplastics other than the protocol treatment (including immunotherapy) and use of TS-1 or UFT during follow-up

2) Use of the antifungal flucytosine, phenytoin, and warfarin (during the protocol treatment)

3) Therapies that must be used with caution with TS-1 and UFT (radiotherapy, hyperthermia, immunotherapy, and hormones)

4) Use of investigational drugs

7.5.2. Permitted concomitant therapy

1) Concomitant use of medications for complications such as hypertension

2) Concomitant use of the following therapies not approved as antineoplastic therapy by the Japanese Ministry of Health, Labour and Welfare

a) Crude drugs such as hochu-ekkito, ninjin-yoeito, and juzen-taihoto

b) Dietary supplements such as agaricus, Phellinus linteus, Ganoderma lucidum, and shark cartilage

7.5.3. Recommended supportive therapies

The following supportive therapies will be recommended. However, not performing them will not be a protocol deviation.

1) WBC (leukocytes decreased): G-CSF

2) Hepatic disorders: liver protective agents, corticosteroid therapy, glucagon-insulin therapy, plasmapheresis, and intravenous amino acid solution

3) Serious renal disorders: Fluid management, electrolyte supplementation, renal dialysis

4) Serious enteritis or symptoms of dehydration: parenteral fluids, antidiarrheals, loperamide

5) Nausea, vomiting: antiemetics, minor tranquilizers

6) Stomatitis: allopurinol gargle, corticosteroids

7) Infections: antibiotics

7.6. Therapy following protocol treatment

This protocol does not specify any therapy after discontinuing the protocol treatment at relapse or developing secondary cancer. However, after discontinuation of the protocol treatment for other reasons and after completion of the protocol treatment, antineoplastics will not be administered until relapse or secondary cancer occurs or until 3 years have elapsed from enrollment of the last subject.

# Adverse Event Evaluation and Reporting

8.1. Definition of adverse event

An adverse event (AE) is any undesirable medical event occurring in a subject receiving the protocol treatment. An AE does not necessarily have to show a definite causal relationship with the protocol treatment. Thus, an adverse event is any undesirable or unintended sign (including abnormal clinical laboratory values), symptom, or disease occurring when the protocol treatment is received regardless of the causal relationship to the protocol treatment.

An AE is a serious adverse event (SAE) if it is any of the following.

1. Death

2. Life-threatening

3. Admission to a hospital or clinic or prolongation of admission that is necessary for treatment

4. Disability/incapacity

5. An event that may result in disability/incapacity

6. Any other serious event consistent with 1-5.

7. Congenital diseases or abnormalities in subsequent generations

8.2. Evaluation of adverse events

AEs observed during or within 30 days after completion of the protocol treatment will be evaluated according to the schedule in “9.2. Observation, test, and reporting schedule.” The maximum severity of each AE during each cycle will be recorded in the case report form.

The AEs observed will be evaluated according to the JCOG/JSCO Japanese-language version of the Common Terminology Criteria for Adverse Events (CTCAE) v.3.0. AEs will be graded according to the definitions (Grade 0-4) that most closely fit the event.

AEs for which a causal relationship to the drug cannot be ruled out will be considered adverse drug reactions.

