Symptom terminology: Fatigue (malaise), weight loss, rash/desquamation, hyperpigmentation, anorexia, diarrhea, mucositis/stomatitis, nausea, vomiting, other (Remarkable events will be recorded.)

Grade: The highest grade during each case report form preparation period will be recorded.

Causal relationship: Yes, No

Confirmation of relapse and secondary cancer

Diagnostic imaging or pathological tests will be performed to confirm the presence of relapse or secondary cancer every 3-6 months after initiation of the protocol treatment. However, appropriate tests will be performed whenever relapse or secondary cancer is suspected from clinical symptoms or the like.

Presence of relapse (If present, the following items will be entered in the outcome report.)

Relapse site: local, distant (brain, bone, lung, liver, lymph node, adrenal gland, skin, other)

Confirmation method and date confirmation performed: simple chest radiography, ultrasonography, CT, MRI, PET, histopathology, cytology, other

Confirmation date (If diagnosed by multiple diagnostic methods, the date the earliest test was performed.)

Presence of secondary cancer (If present, the following items will be entered in the outcome report.)

Site of occurrence of secondary cancer (head and neck, lung, esophagus, stomach, other)

Diagnostic method and date diagnosis performed: simple chest radiography, ultrasonography, CT, MRI, PET, histopathology, cytology, other

Date of diagnosis (If diagnosed by multiple diagnostic methods, the date the earliest test was performed.)

*The presence of relapse and secondary cancer will be confirmed in accordance with “Definition of relapse and secondary cancer” in 11.1.

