9.1.3. At follow-up

1) Testing dates

The observations and tests listed below will be performed every 3-6 months, counting from the first day of the protocol treatment. Follow-up will be performed for 3 years after the enrollment of the last subject. Entries in case report forms will be made once annually until Year 3, after which all tests and observations will be performed 3 years after the enrollment of the last subject.

2) Observations and tests

Outcome

Confirmation of outcome: Survival (date of last confirmation of survival)

Death (Cause of death: primary disease, other cancer, other, date of death)

Lost to follow-up (date of last confirmation of survival)

Method of confirmation: clinic appointment, other

*When survival status cannot be confirmed directly because the subject transferred to another hospital or the like, every effort will be made to obtain outcome information from the subject’s new hospital.

Confirmation of relapse and secondary cancer

Presence of relapse (If present, the following items will be entered in the outcome report.)

Relapse site: local, distant (brain, bone, lung, liver, lymph node, adrenal gland, skin, other)

Confirmation method and date confirmation performed: simple chest radiography, ultrasonography, CT, MRI, PET, histopathology, cytology, other

Confirmation date (If diagnosed by multiple diagnostic methods, the date the earliest test was performed.)

Presence of secondary cancer (If present, the following items will be entered in the outcome report.)

Site of occurrence of secondary cancer (head and neck, lung, esophagus, stomach, other)

Diagnostic method and date diagnosis performed: simple chest radiography, ultrasonography, CT, MRI, PET, histopathology, cytology, other

Date of diagnosis (If diagnosed by multiple diagnostic methods, the date the earliest test was performed.)

*Presence of relapse and secondary cancer will be confirmed in accordance with “Definition of relapse and secondary cancer” in 11.1.

Therapy following protocol treatment: Presence of therapy following protocol treatment

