11.2.3. Adverse events

AEs will be graded according to the JCOG/JSCO Japanese-language version of CTCAE v.3.0.

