# Independent Data Monitoring Committee

The independent data monitoring committee will evaluate the reports listed below at the request of the lead investigator and will provide recommendations to the lead investigator on protocol amendments (refer to “16. Protocol Amendments”) or early termination of the study (refer to “16.2 Early Termination of the Study”).

1) Study progress reports and study monitoring reports from the lead investigator (annually)

2) The interim analysis report from the statistician (1 year after enrollment of the last subject)

3) Serious adverse event reports sent from the lead investigator (as needed)

4) Relevant reports not from this study such as academic articles and presentations (as needed)

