17.2. Early termination of the study

17.2.1. Rules for early termination of the study

The study will be terminated early in the following cases.

1) As a result of evaluating study progress reports from the lead investigator and study monitoring reports, it is concluded that completion of the study is compromised by slow enrollment, frequency of protocol deviations, or the like.

2) Interim analysis confirms the superiority of the test treatment’s efficacy.

3) Interim analysis confirms the inferiority of the test treatment’s efficacy.

4) Adverse events satisfying the following criteria are observed, and it is determined that there are problems with the safety of the protocol treatment.

∙ Protocol-treatment-related deaths 10 subjects

∙ Protocol-treatment-related serious adverse events, including deaths 25 subjects

∙ Protocol-treatment-related Grade 4 neutropenia 25 subjects

5) It is concluded that there are problems with the safety of the protocol treatment as a result of evaluating related information obtained from other studies, scholarly articles, academic conferences, or the like, or it is concluded that continuation of the study is no longer significant.

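### Neither the Grade 0–4 adverse-event scale nor the cause-of-death code can record a treatment-related death, so the stopping count of 10 such deaths has no direct check in the routine data

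*Protocol*

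**What the plan says.** Five parts of the protocol bear on this.

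- **Grading (8.2).** "AEs will be graded according to the definitions (Grade 0-4) that most closely fit the event". The endpoint definition in 11.2.3 names the same dictionary without restating a range: "AEs will be graded according to the JCOG/JSCO Japanese-language version of CTCAE v.3.0".
- **Serious events (8.1).** The list introduced by "An AE is a serious adverse event (SAE) if it is any of the following" gives death as item 1 and life-threatening as item 2, so the two are separate categories.
- **Causality (8.2 and 9.1.2).** Section 8.2 sets the standard: "AEs for which a causal relationship to the drug cannot be ruled out will be considered adverse drug reactions". The item collected for adverse events is "Causal relationship: Yes, No".
- **Outcome report (9.1.3).** The entry for a death reads "Death (Cause of death: primary disease, other cancer, other, date of death". No option attributes the death to protocol treatment.
- **Early termination and monitoring (17.2.1 and 13).** One safety criterion is "Protocol-treatment-related deaths 10 subjects". A second counts 25 subjects with related serious events, deaths included. The monitoring committee receives "Serious adverse event reports sent from the lead investigator (as needed".

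Adverse events are a secondary endpoint (Objective, 11.2.3), and 12.3.2 compares their incidence between arms.

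**The concern.** The protocol treats fatal toxicity as a distinct category in two places: the seriousness criteria and the early-termination criteria. The two routine fields where a reader would look for it, severity grade and cause of death, have no value for it. Section 8.2 states the grading range as a rule. Followed as written, it gives a fatal event a grade that describes a survived one. This is not a detail left open for the analysis plan.

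Two things are at stake. The first is the reliability of a small safety count that can lead to termination of the trial. The second is how clearly fatal toxicity shows in an open-label comparison of two active drugs, wherever adverse events are summarised by grade.

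**Working it through.** The protocol gives no figure to reproduce here, so the check compares what 17.2.1 needs with what the forms can hold.

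**Step 1. What the count needs.** A protocol-treatment-related death requires three facts: the subject died, an adverse event caused the death, and that event was related to treatment.

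**Step 2. What each routine item supplies.**

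| Item | Section | Death? | Attribution to treatment? |
| --- | --- | --- | --- |
| Adverse-event grade | 8.2, 9.1.2 | No, range ends at 4 | No |
| Adverse-event causality | 9.1.2 | No | Yes, for the event but not for the death |
| Cause of death | 9.1.3 | Yes | No, a toxic death falls under *other* |
| Date of death | 9.1.3 | Yes | No |
| Discontinuation reason and date | 7.3, 9.1.2 | Yes, if on treatment | No |

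**Step 3. Can the items be combined?** The adverse-event items listed in 9.1.2 are term, highest grade in the reporting period, and causality. No onset date, outcome or link to a death is listed. The reports fall at about 12, 24 and 52 weeks in the TS-1 arm, so the periods are 12, 24 − 12 = 12 and 52 − 24 = 28 weeks. The UFT schedule is 3, 6 and 12 months.

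Take two subjects. In the same period each has one related and one unrelated Grade 4 event, and each dies on treatment. The first dies of the related event, the second of the unrelated one (not cancer). Their entries in the listed fields can be identical:

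| Field | First subject | Second subject |
| --- | --- | --- |
| Event 1 | Grade 4, causality Yes | Grade 4, causality Yes |
| Event 2 | Grade 4, causality No | Grade 4, causality No |
| Discontinuation reason | Death | Death |
| Cause of death | Other | Other |

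Only the first belongs in the 17.2.1 count. The routine items confirm that a death occurred but do not attribute it. If toxic deaths are coded under *other*, the routine data bound the related count only between zero and the number of *other* deaths.

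**Step 4. The serious-event route.** Section 8.1 separates death from life-threatening events, 9.1.4 sets serious-event reporting apart from the routine forms, and section 13 sends the reports to the committee. This route can supply the count.

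**Step 5. Scale.** The planned size is 500, with 250 per arm (10.1).

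- Limit for related deaths: 10/500 = 2.0% of all subjects, or 10/250 = 4.0% of one arm if all fell there.
- Limit for related serious events: 25/500 = 5.0%, or 25/250 = 10.0% of one arm.
- One misattributed death: 1/10 = 10% of the limit for deaths.
- Expected related deaths at assumed true rates (the protocol gives none): 500 × 0.005 = 2.5, 500 × 0.01 = 5, 500 × 0.02 = 10.

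**The case against.** The strongest reply is that the early-termination rule has its own data source. Serious-event reports distinguish a death from a life-threatening event, and 17.2.1 itself treats related deaths as a subset of related serious events. The outcome report is also a slow source: 9.1.3 has it entered once a year up to Year 3. All of this stands. A reader might infer that related deaths cannot be counted from the trial's data at all, but serious-event reports are trial data and can supply the number.

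Two other stronger readings also fail.

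- A reader might infer that the tables in 12.3.2 would show toxic deaths as Grade 4 events. That section specifies tabulation by arm and type and does not mention grade, so the merging arises only where a summary by grade is produced.
- A reader might infer that the survival analyses are damaged. DFS, RFS and OS all use death from any cause (section 11), and no cause-specific analysis is stated. A different cause-of-death code would change none of them.

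It can also be said that 11.2.3 cites the grading dictionary without the 0–4 limit, so the parenthesis in 8.2 may be loose wording. That is possible, but 8.2 is the operative instruction and it is explicit.

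The argument that date of death, discontinuation reason and adverse-event records already permit reconciliation stands only in part. As step 3 shows, they reconcile the fact of death but not its attribution.

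**Conclusion.** The point holds in a narrow form. The grading rule in 8.2 and the cause-of-death list in 9.1.3 each lack a value for treatment-related death, and the other listed items do not make good the gap. The count of 10 (2.0% of 500) therefore rests on serious-event reports, with no routine field to check their attribution. Any summary by grade would place fatal and survived events together in Grade 4. No endpoint definition, sample size or error rate is affected, and nothing here shows that a count has been lost. The gap is modest in consequence, but it comes from a stated rule, concerns a secondary endpoint and is cheap to close.

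The conclusion rests on the fields listed in the protocol. The content of the serious-event form and any free text beside *other* are not visible. Section 9.1.2 limits web reporting to underlined items and the underlining is not preserved, so it cannot be confirmed that the causality item is reported. If it is not, the routine data carry still less attribution. The visible part of section 8 contains no reporting procedure. That may be an effect of text extraction, and the conclusion does not depend on it.

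**What to change.** 1. In 8.2, extend the grading range to include a fatal grade, for death related to the adverse event.
2. In 9.1.3 and the outcome report, add a protocol-treatment-related option for cause of death, or an explicit link from the death to the adverse event that caused it.
3. In 17.2.1, define a protocol-treatment-related death, using the causality standard already in 8.2. Keep serious-event reports as the primary source for the count, and reconcile them with the two fields above before each report to the monitoring committee.
4. Report fatal adverse events separately by arm.

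The cost is one grade and one code on existing web forms, a short amendment, and re-coding of deaths already entered. One knock-on needs a sentence. Section 17.2.1 also counts related Grade 4 neutropenia (25 subjects), so once a fatal grade exists the text should say whether a fatal case is still included in that count. The change alters no dose, schedule or treatment rule.

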# Observations, Tests, Reported Parameters, and Schedule

9.1. Observation and test parameters, and treatment information to be reported

9.1.1. Before enrollment (confirmation of eligibility) and baseline parameters

1) Information obtained before enrollment (entered in the enrollment form)

Basic patient information

Date of birth, age at consent (can be automatically calculated from date of birth and date of consent), sex, height at consent, weight at consent, body surface area at consent (can be automatically calculated from height and weight), date of written informed consent

Information on disease to be treated

Histological diagnosis: Squamous cell cancer

Primary site: Maxillary sinus, oral cavity, oropharynx, hypopharynx, larynx (except T3N0 of the glottis)

Baseline Stage: III, IVA, IVB

TNM staging: T(1, 2, 3, 4a, 4b), N(0, 1, 2, 3), M(0)

Curative therapy information

First curative therapy: surgery (date of surgery), radiotherapy (radiation duration and total dose), completion date of first curative therapy

Other concomitant therapy: Yes / No (If “Yes,” surgery, radiotherapy, chemotherapy [fluoropyrimidines, platinating agents, other ]),

Tumor eradication confirmation date, means of tumor eradication confirmation (diagnostic imaging, histopathology, cytology)

ECOG performance status scale: PS (0, 1)

Clinical laboratory tests (Test results obtained within 14 days before enrollment will be used.)

Test date

Hematology: WBC, Neut, PLT, Hb

Blood biochemistry: T.Bil, AST (GOT), ALT (GPT), Cr, albumin*, LDH*, ALP*, Na*,

K*, Ca*, CRP* Parameters marked with an asterisk will be entered into the baseline report.

Current medical history: Presence of infections, presence of gastrointestinal disorders, presence of interstitial pneumonia and/or pulmonary fibrosis, presence of diabetes mellitus, presence of heart disease, presence of hepatic disorders, presence of diarrhea (watery stools)

2) Baseline information (to be entered into the baseline report)

Recent cancer history: Presence of previous disease, diagnosis, year of diagnosis

Concurrent / previous disease besides cancer: Diabetes mellitus, hypertension, hyperlipidemia, coronary artery disease, stroke, other

Signs and symptoms (The highest grade in the 14 days before beginning the protocol treatment will be confirmed.):

Fatigue (malaise), weight loss, rash/desquamation, hyperpigmentation, anorexia, diarrhea, mucositis/stomatitis, nausea, vomiting, other (Remarkable signs and symptoms will be recorded.)

If the following parameters are measured, results obtained in the 30 days prior to enrollment will be used.

Tumor markers: Date performed, assay values (SCC or CYFRA)

Protocol treatment initiation date

Actual dose administered

9.1.2. During the study period

1) Testing dates

(1)TS-1-treated arm (experimental treatment arm)

The observations and tests listed below will be performed on the first dosing day (Day 1) and Day 8 of the first cycle and on the first day of the second and all subsequent cycles. The results will be entered in the case report forms via the web at the fourth and eighth cycles and at completion of treatment after 1 year.

(2)UFT-treated arm (control treatment arm)

The observations and tests listed below will be performed on the first dosing day (Day 1), Day 8, and Day 29 during the first 4 weeks and then every 4 weeks, starting at Week 5. The results will be entered in the case report forms via the web at 3, 6, and 12 months (completion of treatment).

2) Observations and tests: The following tests will be performed on the prescribed testing days.

Note that only the underlined data below will be reported via the web.

ECOG performance status scale: PS

Test parameters related to the study drugs

Compliance*: Compliance will be confirmed based on the medication record and scored on the following scale. The investigator will score compliance on the following 4-grade scale every 4 cycles for TS-1 and every 3 month for UFT.

*The percentage of drug taken during the dosing period will be calculated. Note that the number of capsules not taken during the rest period will not be included in the calculation.

(1) Took 100% (2) Took ≥ 75% and < 100%, (3) Took ≥ 50% and < 75%, (4) Took < 50%

Rest: presence of rest, reason for rest,

duration of rest (rest initiation date and treatment resumption date)

Dose reduction: presence of dose reduction, reason for dose reduction, daily dose after reduction

Discontinuation: presence of discontinuation, discontinuation date, reason for discontinuation

Submission of follow-up data after withdrawal of consent: possible, not possible

Clinical laboratory tests

Hematology: WBC, Neut, PLT, Hb

Blood biochemistry: T.Bil, AST, ALT, Cr, LDH*, ALP*, CRP*, Na*, K*, Cl*, Ca*

*Will be done when possible

(Only WBC, Neut, PLT, Hb, T.Bil, AST, ALT, and Cr will be entered in the record; the presence of adverse events in each test and the highest grade will be entered.)

Tumor markers: SCC or CYFRA

(Will be measured if necessary. Results will be entered via the web if measured within 30 days before or after discontinuation or completion of protocol treatment.)

Adverse events

Symptom terminology: Fatigue (malaise), weight loss, rash/desquamation, hyperpigmentation, anorexia, diarrhea, mucositis/stomatitis, nausea, vomiting, other (Remarkable events will be recorded.)

Grade: The highest grade during each case report form preparation period will be recorded.

Causal relationship: Yes, No

Confirmation of relapse and secondary cancer

Diagnostic imaging or pathological tests will be performed to confirm the presence of relapse or secondary cancer every 3-6 months after initiation of the protocol treatment. However, appropriate tests will be performed whenever relapse or secondary cancer is suspected from clinical symptoms or the like.

Presence of relapse (If present, the following items will be entered in the outcome report.)

Relapse site: local, distant (brain, bone, lung, liver, lymph node, adrenal gland, skin, other)

Confirmation method and date confirmation performed: simple chest radiography, ultrasonography, CT, MRI, PET, histopathology, cytology, other

Confirmation date (If diagnosed by multiple diagnostic methods, the date the earliest test was performed.)

Presence of secondary cancer (If present, the following items will be entered in the outcome report.)

Site of occurrence of secondary cancer (head and neck, lung, esophagus, stomach, other)

Diagnostic method and date diagnosis performed: simple chest radiography, ultrasonography, CT, MRI, PET, histopathology, cytology, other

Date of diagnosis (If diagnosed by multiple diagnostic methods, the date the earliest test was performed.)

*The presence of relapse and secondary cancer will be confirmed in accordance with “Definition of relapse and secondary cancer” in 11.1.

